## Effects to be estimated

### 9.2.1 Primary Endpoint:

RVIP accuracy score

### 9.2.2 Secondary Endpoint:

The secondary endpoints concerned are:

- Inspection Time – time that target is correctly identified in 80% of trials
- Serial Sevens - total number of subtractions and number of errors
- Serial Threes - total number of subtractions and number of errors
- Emotional face recognition task – percent of correctly recognised emotions
- N-back task - speed and accuracy
- Reaction Time – mean reaction time (ms)
- Bond and Lader Visual Analogue Scales
- Caffeine Research Visual Analogue Scales
- Brain doppler blood flow - mean velocity

Same comparison as primary objective on secondary outcomes:

Assess the effect of CGA vs. placebo on secondary outcomes.

Other comparisons of interest:

Assess the effect of CGA vs. decaffeinated coffee on primary and secondary outcomes.

Assess the effect of decaffeinated coffee vs. placebo on primary and secondary outcomes.

## 9.3 Sample size calculation

With the above estimated effect size and with-in standard deviation, 58 subjects would be needed in the crossover study. With a dropout rate of 10% (as also suggested in 08.17.NRC, 4/43), the total number of subject to be enrolled is 66.

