In a recent trial conducted by Swinburne University and Nestlé, it was found that 3 servings of regular decaffeinated coffee had little or no effect on cognitive function and mood in a healthy older population, thus suggesting that coffee compounds found in regular coffee do not modulate cognitive function or mood. However, the results did indicate that 3 servings of a specially processed decaffeinated coffee exerted positive trend-level acute effects on cognition (specifically attention) and mood (increasing alertness and relaxation, and decreasing reports of mental fatigue and headaches). These findings suggest that there are compounds (other than caffeine) in this specially processed decaffeinated coffee that appear to have positive effects on cognitive function and mood that are not found or that are not at the same level as that found in regular coffee. As chlorogenic acids (CGA) are the most abundant family of compounds found in this specially processed decaffeinated coffee, it is possible that the positive cognitive and mood effects observed are attributed to the chlorogenic acids. To further explore this possibility, the present study aims to assess the effect of pure chlorogenic acid on cognitive function and mood in a healthy older population. The chlorogenic acid will be derived from coffee and the dose to be administered will be the same as is found in 6g of this specially processed decaffeinated coffee. To further understand whether it is the CGAs in the specially processed decaffeinated coffee that are attributed to the positive effects, a second aim is to compare the effects of pure CGA with the decaffeinated coffee. If it is the CGAs contributing to the positive effects, it is expected that there should be no difference in cognitive performance and mood between pure CGA and decaffeinated coffee.

Finally, as the results from the initial acute clinical trial are the first indication that a non-caffeinated pure coffee may improve cognitive performance, the study findings need to be replicated and confirmed. Thus, the third aim is to replicate and confirm the previous trend-level findings and show that 6g decaffeinated coffee improves attention and mood in a healthy older population.

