# Statistical aspects and considerations

## 9.1 Background

The primary objective suggested for this trial is to evaluate the effect of acute CGA on attention in terms of performance on the Rapid Visual Information Processing (RVIP) task. In particular, the Total Number of correct Hits, the Reaction Time for the Correct Hits and the False Alarm Rate have been specified. We use the data from a previous trial (08.17.NRC) to estimate the effect sizes and to calculate the sample size needed to have 80% power to detect these effects. In particular, we use the 08.17.NRC data from the Placebo and Decaffeinated Coffee from Green Beans (which is abundant in CGA). The RVIP task consists of identifying targets (sets of 3 consecutive odd/even numbers) out of 96 possible targets. Thus theoretically speaking, this is a binomial trial for each subject with size=96. The success rate is estimated (using data from the placebo group in Trail 08.17.NRC) to be p = 63/96 = .656 which is moderate to large. Thus we expect the data to be fairly Normally distributed. A mixed analysis of covariance (ANCOVA) model was fit to the placebo and decaf coffee from green beans data from the 08.17.NRC trial. The normality and homoscedasticity assumptions were checked. The estimated effect size was an increased score of 2.45 points on the RVIP as compared to placebo and the with-in standard deviation was estimated to be 6.52.

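### The 80% power claimed for 58 subjects holds only if 6.52 is the SD of the treatment contrast; read as the within-subject SD of a score, power for 2.45 hits is between 51% and 80%

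*Protocol*

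**What the plan says.** Protocol section 9.1 uses data from trial 08.17.NRC "to calculate the sample size needed to have 80% power to detect these effects". The source of the inputs is described thus: "A mixed analysis of covariance (ANCOVA) model was fit to the placebo and decaf coffee from green beans data from the 08.17.NRC trial". The estimated effect was an "increased score of 2.45 points on the RVIP as compared to placebo", and "the with-in standard deviation was estimated to be 6.52". The same section treats the RVIP score as binomial, with 96 targets and a success rate of 63/96 = 0.656.

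Section 9.3 then concludes: "With the above estimated effect size and with-in standard deviation, 58 subjects would be needed in the crossover study". Allowing for 10% dropout, it enrols 66.

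The protocol gives no alpha, sidedness or formula. It does not say whether 6.52 belongs to one score or to a difference between treatments, or how many post-dose scores the calculation assumes. Section 8.5 schedules two post-dose test batteries per session (40 and 120 minutes). Section 9.5 plans a baseline-adjusted mixed model with a random subject intercept, time and treatment, and their interaction only if needed.

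**The concern.** In a mixed model, a within SD ordinarily means the residual SD of a single score within a subject. A crossover comparison rests on the difference between two treatments in the same subject. If each treatment contributes one score, that difference has an SD larger by a factor of √2. Entering a per-score SD where the SD of a difference belongs halves the variance and roughly halves the sample size.

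Sections 9.1 and 9.3 are the only justification for the size of the trial. If the true power for 2.45 hits is well below 80%, a null CGA-placebo result would be read as evidence against CGA when the trial had a sizeable chance of missing the effect it was planned to detect.

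**Working it through.** **Inputs.** From section 9.1: effect δ = 2.45, s = 6.52, power 80%, 96 targets, p = 0.656. From section 9.3: n = 58, enrolled 66, and 4 dropouts of 43 in 08.17.NRC. From section 8.5: two post-dose scores per session. Assumed because none is stated: two-sided alpha 0.05 (one-sided 0.05 as the alternative), and a same-session correlation ρ of 0.2 to 0.5, with 0 and 1 as bounds.

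**Step 1: reproduce 58.** Take 6.52 as the SD of the paired difference.
- Normal approximation: n = ((1.960 + 0.842) × 6.52 / 2.45)² = 55.6, so 56.
- Paired t with the noncentral t distribution: n = 58, power 80.3%.

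The stated figure is exactly this answer.

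**Step 2: 6.52 as a per-score SD, one score per treatment.** SD of the difference = √2 × 6.52 = 9.22.
- Normal approximation: (2.802 × 9.22 / 2.45)² = 111.2, so 112. Paired t: 114.
- At n = 58 the noncentrality is 2.45 / (9.22/√58) = 2.02. Power is 51% (57% at n = 66).
- With one-sided 0.05, power at 58 is 64%.
- The difference detectable with 80% power at 58 is 3.45 hits.

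**Step 3: 6.52 as a per-score SD, two post-dose scores averaged.** Let ρ be the correlation between the within-subject deviations of two scores from the same session. Then

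SD of contrast = √(2 × s² × (1 + ρ)/2) = s × √(1 + ρ).

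| ρ | SD of contrast | Power at 58 | n for 80% |
|---|---|---|---|
| 0 | 6.52 | 80% | 58 |
| 0.2 | 7.14 | 73% | 69 |
| 0.5 | 7.99 | 63% | 86 |
| 1 | 9.22 | 51% | 114 |

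At ρ = 0, averaging cancels the √2 exactly and 58 returns. At ρ = 1 the second score adds nothing and step 2 returns.

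**Step 4: could 6.52 be the SD of a difference between two single scores?** Under the protocol's own binomial model, the noise SD of one score is √(96 × 0.656 × 0.344) = 4.65. The difference of two scores therefore has a noise SD of at least √2 × 4.65 = 6.58, already above 6.52 with no session-to-session variation allowed for. If p varies between subjects with an SD of 0.10 (assumed), the floor is √(2 × 96 × (0.2256 − 0.01)) = 6.43, which still leaves almost no room. So 6.52 is unlikely to be that SD. For a difference between means of two scores the floor is 6.58/√2 = 4.65, so this argument does not exclude 6.52 as an SD of that kind.

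**Step 5: the earlier trial's result.** The Introduction says that the specially processed coffee "exerted positive trend-level acute effects on cognition (specifically attention" and mood. Assume 43 − 4 = 39 subjects in a simple paired comparison.
- SD 9.22: t = 2.45/(9.22/√39) = 1.66, p = 0.105.
- SD 6.52: t = 2.45/(6.52/√39) = 2.35, p = 0.024.

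The first fits a trend better than the second, but this is supporting evidence only.

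**The case against.** A reader might infer that the protocol contains a plain arithmetic error and that the trial has 51% power. The documents do not support that. With 2.45 and 6.52 as the paired-difference inputs, 58 is exactly right. There is also a route to 58 that keeps 6.52 as a per-score SD: the model in section 9.5 has only a subject intercept, treats residuals as independent given the subject, and, without the interaction, averages the treatment effect over both post-dose times. That is the ρ = 0 row. The figure of 51% needs one score per treatment or a same-session correlation of 1, and the protocol states neither. Baseline is retaken at each session (section 8.4), and adjusting for it may remove some shared session-day variation.

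The history check is also weak. The Introduction describes attention and mood together, gives no p-value and does not name RVIP accuracy. The number of subjects and time points behind the 2.45 is not given, nor is any multiplicity adjustment in that trial. Alpha is an assumption here, and the objective is worded directionally.

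All of this stands against the flat claim, but it does not rescue the 80%. Independence between two tests taken in one session, after the same drink, night's sleep and meal, is the most favourable case. A random subject intercept assumes that independence rather than securing it. Neither section 9.1 nor 9.3 says that two scores were averaged.

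**Conclusion.** The point holds in conditional form. The 80% follows only if 6.52 is the SD of the treatment contrast. That means either the label is wrong, or 6.52 is per score and two post-dose scores count as independent replicates. With 6.52 as the per-score within-subject SD, power at 58 for 2.45 hits runs from 51% to 80%, with 63% to 73% for the assumed correlations of 0.5 to 0.2. Correspondingly, the difference detectable at 80% power may be as large as about 3.45 hits. These figures assume two-sided alpha 0.05; under one-sided 0.05 the lowest case is 64%.

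Which reading is right cannot be settled from the protocol. The binomial floor makes a difference of two single scores unlikely. The trend-level wording only leans the same way. This should be corrected because it changes what a null result can mean, but it does not show that the sample size is wrong. The enrolment of 66 is not in question: 58/0.9 = 64.4, so 65, and 66 is a multiple of the six sequences of a three-treatment Williams design.

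**What to change.** Keep 58 completers and 66 enrolled.

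- Recompute from the 08.17.NRC data the SD of the baseline-adjusted treatment contrast that will be tested, letting scores from the same session be correlated.
- State in sections 9.1 and 9.3 that SD, the alpha and sidedness, and the number of post-dose scores averaged.
- Replace the 80% statement by the power, or the difference detectable at 80%, that 58 delivers with that SD. Until it is available, give 51% to 80% for 2.45 hits and a detectable difference of up to about 3.45.
- If 6.52 proves to be the SD of the contrast, relabel it so; the 58 and the 80% then stand at two-sided 0.05.

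The cost is one reanalysis of existing data and rewording of two sections, with no added subjects. The downside is that the stated power may become less favourable.

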## 9.4 Randomization

The products used in this study will be coded (A, B and C). A randomization schedule will be generated using Williams Design in R 2.6.1 using these codes. The randomization schedule will be made available to the investigator by hard copy.

## 9.5 Statistical analysis

9.5.1 Primary Outcome

As mentioned in section 9.1, we expect the accuracy score on the RVIP to be fairly normally distributed, since the Central Limit Theorem applies here. The proposed analysis is a mixed ANCOVA model that adjusts for the baseline scores. The mixed model here will incorporate a subject specific random intercept term which will accommodate for correlated repeated measurements with-in each subject. The main independent variables will be time, treatment and if necessary their interaction.

During the blind review and prior to data freezing and code breaking, the feasibility of the above proposed analysis plan will be verified using the blinded data. In case the above proposal is deemed not feasible, alternative methods like using normalizing transforms or non-parametric methods will be proposed in the updated final statistical analysis plan.

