**V1 (Week 2)**

- Safety assessment recorded in CRF (adverse event record)
- Mood visual analogue scales (Bond-Lader Visual Analogue Scales & Caffeine Research Visual Analogue Scales) will be completed six times (immediately before and after cognitive testing at baseline, 40 minutes and 120 minutes post treatment consumption)
- Cognitive testing will be completed three times (baseline, 40 minutes and 120 minutes post treatment consumption). Specifically:

- Emotional face recognition task

- Jenson Box reaction time task

- Inspection Time task

- Serial sevens

- Serial threes

- N-back task

- Rapid Visual Information Processing task

- Bond and Lader Visual Analogue Scales

- Caffeine Research Visual Analogue Scales

- Blood sample (three times: 10, 90 and 160 minutes post treatment consumption)
- Brain doppler blood flow (baseline and 90 minutes post treatment consumption)

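### Protocol 9.5.1 relies on a subject random intercept alone, which makes the standard error too small for a treatment effect pooled over the two post-dose scores of each session

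*Protocol*

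**What the plan says.** Section 8.4 has a baseline taken at the start of every testing session. Section 8.5 gives the test times for each of V1 to V3: "Cognitive testing will be completed three times (baseline, 40 minutes and 120 minutes post treatment consumption". Section 9.4 randomises the order of the three products by a Williams design, so one product belongs to one session. Each subject therefore gives three randomised units, three baselines and six post-dose RVIP accuracy scores.

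Section 9.5.1 (Primary Outcome) proposes a mixed ANCOVA adjusted for baseline. Of its random part it says: "The mixed model here will incorporate a subject specific random intercept term which will accommodate for correlated repeated measurements with-in each subject". Of its fixed part it says: "The main independent variables will be time, treatment and if necessary their interaction". It names no session or visit effect and no within-session covariance. A blind review before code breaking is to check that the plan is feasible; the alternatives it mentions are normalising transforms and non-parametric methods. Section 9.5.2 carries similar models over to the secondary outcomes.

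**The concern.** A subject intercept captures how subjects differ from one another. It cannot capture that two scores from the same day, after the same drink and adjusted by the same baseline measurement, are more alike than two scores from different days. Because treatment changes only between sessions, that extra likeness goes straight into the true variance of the treatment contrast. The fitted model does not see it.

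At stake are the primary p-value and confidence interval. Section 2 of the protocol presents the trial partly as confirmation of trend-level findings from the previous study, so an understated standard error on the primary test could turn another trend into a claim.

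**Working it through.** **Inputs from the protocol.** Three sessions per subject; one baseline and two post-dose scores per session (8.4, 8.5); effect 2.45 points and SD 6.52 (9.1); 80% power (9.1); 58 completers (9.3). **Assumed, because not stated:** a two-sided 5% level, the between-subject variance and the session variance.

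**1. The plan's own figure.** Section 9.1: "The estimated effect size was an increased score of 2.45 points on the RVIP as compared to placebo" and "with-in standard deviation was estimated to be 6.52". Section 9.3: "58 subjects would be needed in the crossover study". Taking 6.52 as the SD of a paired difference, n = (6.52 × (1.960 + 0.842) / 2.45)² = 55.6, so 56 by the normal formula. The paired t-test gives 58, with power 80.3%. The figure reproduces.

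**2. Direction of the error.** Let σ² be the within-subject variance of a post-dose score after adjustment, and ρ the correlation between the two scores of one session beyond the subject effect.

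- The difference between two session means has true variance proportional to σ²(1 + ρ).
- The intercept-only model uses one pooled within-subject mean square. Per subject that is 2 degrees of freedom between sessions with expectation σ²(1 + ρ), and 3 within sessions with expectation σ²(1 − ρ). The pooled value is σ²[2(1 + ρ) + 3(1 − ρ)]/5 = σ²(1 − 0.2ρ).
- For the effect pooled over both times, model SE / true SE = √[(1 − 0.2ρ)/(1 + ρ)].
- For a contrast read at one time from an interaction model, only one score per session enters, and the ratio is √(1 − 0.2ρ).
- The actual error rate is about 2Φ(−1.96 × ratio).

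| ρ | pooled: SE ratio | pooled: error rate | single time: SE ratio | single time: error rate |
|---|---|---|---|---|
| 0.1 | 0.944 | 6.4% | 0.990 | 5.2% |
| 0.3 | 0.850 | 9.6% | 0.970 | 5.7% |
| 0.5 | 0.775 | 12.9% | 0.949 | 6.3% |

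**3. Why there is inflation even without a day effect.** Set the error variance to 1. If one common baseline slope β is fitted, it is pulled up by between-subject differences. Each adjusted post-dose score then carries −β times the same baseline error, so ρ = β²/(1 + β²). In simulation β averaged 0.30 and 0.44 when subject variance was 2 and 5 times error variance. That gives ρ = 0.09/1.09 = 0.083 and 0.194/1.194 = 0.162, and predicted error rates of 6.2% and 7.4%. The simulated rates were 5.7% and 7.8%.

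**4. Simulation of the model as written.** REML, no treatment effect, 60 subjects, one common baseline slope, test pooled over both times. Three sets were run with different assumptions.

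| Assumptions | No session variance | With session variance | Session as the unit |
|---|---|---|---|
| Within-subject SD 6.52, between-subject SD 8 or 15, session share 0.2 or 0.4 of within-subject variance (4,000 runs per cell) | 5.8%, 7.0% | 9.0% to 11.4% | 4.3% to 5.8% |
| Subject variance 2 to 10 times error variance, session variance 0.25 to 2 times (2,500 to 3,000 runs) | 5.7% to 9.5% | 7.8% to 12.2% | 4.0% to 5.4% |
| Within-subject SD 6.52, session share 0.2 to 0.4 (1,500 runs) | 6.9% to 8.5% | 7.9% to 12.8% | not tabulated |

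In the second set, extra session variance confined to the post-dose scores raised the rate to as much as 14.6%. Model SE / true SE ran from 0.95 down to 0.74. Treating the session as the unit made the SE 1.09 to 1.33 times that of the written model, in line with the true sampling variation. Reading treatment at one time from an interaction model gave 4.5% to 6.8%.

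**5. Splitting the baseline** into the subject's mean and the session's deviation from it. With no session variance the error rate falls to 5.1% to 5.2%. With session variance it is still 6.6% to 9.7%. At session share 0.2 the true SD of the contrast falls from 0.963 to 0.894 (between-subject SD 8) and from 1.089 to 0.892 (SD 15). The variance reductions are 1 − (0.894/0.963)² = 14% and 1 − (0.892/1.089)² = 33%.

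**The case against.** The protocol does not say that the subject intercept is the only random term, it calls the analysis proposed, and it foresees a final analysis plan that could add a session term. The blind review could estimate within-session correlation without the treatment codes, and its listed alternatives read as examples. This stands to the extent that the structure can still be changed. But the protocol does more than leave the covariance open: it names one term and asserts that this term takes care of the correlation, which is incorrect. The review tests feasibility, and this model will fit without difficulty. Neither alternative it mentions deals with correlation.

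A reader might infer that the false-positive rate exceeds 5% whatever is done. The documents do not support that. Section 9.5.1 does not say which contrast is primary, and a single-time contrast from an interaction model stays close to nominal. The inflation without session variance also depends on one common baseline slope, which 9.5.1 does not spell out.

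A reader might also infer that 58 subjects are too few. If 6.52 were the residual SD of a single score, the SD of a difference between session means would be 6.52 × √(1 + ρ). At ρ = 0.2, 0.3 and 0.5 that needs 69, 75 and 86 subjects. The protocol does not say what 6.52 is, and 58 follows exactly if it is the SD of a paired difference, so no error in N is shown.

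Finally, one might ask that treatment-by-time always be fitted. In balanced data this leaves the time-averaged estimate unchanged and does not remove the within-session correlation, so it is no remedy for the pooled test.

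**Conclusion.** Wrong as written. The statement that a subject intercept accommodates the within-subject correlation does not hold for a treatment effect pooled over 40 and 120 minutes, and that effect is the default reading of 9.5.1. The direction is firm: the standard error is too small. The size is conditional. Under a two-sided 5% level and the assumed variance components, the false-positive rate is about 6% to 9% with no session variance (one common baseline slope) and about 8% to 13% with moderate session variance. The protocol gives neither the level nor the components, so these are ranges and not estimates for this trial.

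**What to change.** In 9.5.1, add a random session (subject-by-visit) effect to the subject intercept, or analyse the mean of the two post-dose scores in each session. State that the primary contrast is CGA minus placebo under that model, and carry the same structure to the secondary outcomes that are tested twice per session.

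As a cheap gain in precision, enter baseline as two covariates: the subject's mean and the session's deviation from it. This complements the session term and cannot replace it. Treatment-by-time need not be made compulsory.

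The cost is a sentence or two in the protocol or analysis plan and a few lines of code, before code breaking, with no extra data or subjects. The price is a somewhat wider confidence interval, which is the correct one.

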# Conduct of the trial

## 8.1 Study plan, flow chart

A flow chart of the testing schedule is outlined in Appendix 4.

A short telephone interview will be conducted will all potential subjects to ensure study criteria are met (i.e. see Section 5 Study Population). Successful volunteers will then attend one training session. Note that prior to the training session subjects will be a given a list of foods that need to be avoided prior to the training session. Specifically, subjects will be asked to abstain from caffeine-containing foods and beverages, alcohol, no foods containing chlorogenic acids, and only food with low polyphenol content for 24 hours prior to each testing session. During the training session, subjects will complete demographics and medical questionnaire, the MMSE, and informed consent will be obtained (if criteria are met). Subsequently, subjects will complete the battery of cognitive tests to familiarize subjects with study procedures and minimize procedural learning effects. A baseline blood sample will be obtained.

Approximately 24 hours prior to each testing session, subjects will receive a reminder telephone call that they must abstain from caffeine-containing foods and beverages, alcohol, no foods containing chlorogenic acids, and only food with low polyphenol content for 24 hours prior to each testing session. Subjects are instructed to arrive at the laboratory well rested (following a normal night’s sleep). At the beginning of each experimental session, bread with various spreads and orange juice will be provided. After the participant finishes eating, subjects will complete the mood visual analogue scales followed by the cognitive tests. The mood scales will be completed a second time immediately after baseline cognitive testing is finished. The battery of tests should take approximately 40 minutes to complete. Subsequently, baseline brain doppler blood flow will be obtained. Subjects will then be administered the equivalent of 3 servings of coffee, which must be consumed within 15 minutes.

Based on a previous pharmacokinetic study conducted at Nestlé, following oral ingestion of Nescafé PROTECT coffee, several polyphenol metabolites were shown to peak in plasma within 2 hours after coffee ingestion (Renouf et al., 2008). Based on these results and the results from the acute clinical decaffeinated coffee trial (08.17.NRC), cognitive testing will begin 40 minutes after treatment consumption.

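### The Williams design balances treatments over three visits, but the primary model names no visit term and leaves 'time' undefined; the possible cost is precision, not bias

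*Protocol*

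**What the plan says.** On allocation, section 9.4 states: "A randomization schedule will be generated using Williams Design in R 2.6.1 using these codes". With three treatments this means six sequences, so each drink appears equally often at each visit when sequences are filled equally.

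The primary model in section 9.5.1 (Primary Outcome) is a mixed ANCOVA with the baseline score as covariate and a random intercept for subject. Its factors are given as: "The main independent variables will be time, treatment and if necessary their interaction". Visit (period) is not mentioned. The protocol does not say what 'time' is. Section 8.5 schedules cognitive testing in each session at baseline and at 40 and 120 minutes after consumption. Section 9.5.2 (Secondary Outcome) carries models of the same kind to the other outcomes.

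Two other passages bear on the point. Section 8.4 takes a new baseline at the start of every session. Section 8.1 has subjects run the whole battery once at a training visit, to "familiarize subjects with study procedures and minimize procedural learning effects".

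**The concern.** The Rapid Visual Information Processing (RVIP) task is run once in training and nine times over the three sessions. The training aims to limit learning, not to rule it out. The earlier trial's placebo success rate was 63 of 96 (section 9.1), so scores have room to rise. The effect sought is only 2.45 hits, so a rise of a few hits from visit to visit would be as large as the treatment effect.

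The design makes it possible to separate such a shift from treatment at almost no cost, but the named model does not do so. On the natural reading of 'time', visit is missing. If 'time' meant visit, the 40/120-minute factor would be missing instead. Either way one of two factors that the design calls for is not named, and the error term for the primary comparison may be larger than it needs to be.

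**Working it through.** **1. The plan's own figure.** Inputs from sections 9.1 and 9.3: "The estimated effect size was an increased score of 2.45 points on the RVIP as compared to placebo"; "the with-in standard deviation was estimated to be 6.52"; 80% power; "58 subjects would be needed in the crossover study". Alpha is not stated; 0.05 two-sided is assumed. Normal formula: (6.52 × (1.960 + 0.842) / 2.45)² = 55.6, so 56. The noncentral t gives 58 (power 0.803), so the figure reproduces with 6.52 as the SD of a paired treatment difference. The same SD arises if 6.52 is the within-subject SD of one assessment and two independent post-dose assessments are averaged: √(2 × 6.52²/2) = 6.52. A visit term plays no part in this calculation.

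**2. Outer bound, if baseline absorbed nothing.** Suppose scores rise by g hits per visit. In a balanced three-visit design, two given treatments lie one visit apart in 4 of 6 sequences and two apart in 2 of 6. The mean squared shift is g² × (4×1 + 2×4)/6 = 2g², and the apparent SD is √(6.52² + 2g²).
- g = 1: SD 6.67, power at 58 subjects 0.785
- g = 2: SD 7.11, power 0.733
- g = 3: SD 7.78, power 0.655

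The plan does adjust for session baseline, so these overstate the loss.

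**3. With session baseline in the model.** Assumptions: 60 subjects (a multiple of six near 58); within-subject variance of one assessment σ² = 6.52² = 42.51; a share s of it common to all assessments in a session; outcome = mean of the two post-dose scores. The within-subject slope on baseline is then s. For visit shifts p, let q = Σ(p − mean)²/2.

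*Visit in the model:* residual variance σ²(1+s)/2 − s²σ². For s = 0.2: 25.51 − 1.70 = 23.81, so SE = √(2 × 23.81/60) = 0.891.

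*Visit left out:* slope b = (sσ² + q)/(σ² + q); residual variance σ²(1+s)/2 + q − b(sσ² + q). For s = 0.2 and shifts 0/4/6:
- q = (11.11 + 0.44 + 7.11)/2 = 9.33
- b = (8.50 + 9.33)/(42.51 + 9.33) = 0.344
- residual variance = 25.51 + 9.33 − 0.344 × 17.84 = 28.70, so reported SE = 0.978

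In balanced data the visit shifts cancel out of the treatment contrast. Its true variance uses σ²(1+s)/2 − 2b·sσ² + b²σ² = 25.51 − 5.85 + 5.03 = 24.69, so the true SD is 0.907. The reported SE is therefore too large, and the test is conservative:
- power without visit: Φ((2.45 − 1.98 × 0.978)/0.907) = 0.714
- power with visit: Φ((2.45 − 1.98 × 0.891)/0.891) = 0.779
- type I error without visit: 2Φ(−1.98 × 0.978/0.907) = 0.033

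Simulation of the same setting (6,000 replicates) agrees: SE 0.981 against 0.893, power 0.711 against 0.776, type I error 0.032 against 0.051. In a further run of 4,000 replicates per setting, the mean estimate lay between 2.43 and 2.48 (true value 2.45) with or without the visit term.

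The same formulas over a range of assumptions:

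| Share s | Visit shifts (hits) | Power without visit | Power with visit | Loss (points) |
|---|---|---|---|---|
| 0.2 | 0/0/0 | 77.9% | 77.9% | 0 |
| 0.2 | 0/2/3 | 76.1% | 77.9% | 1.8 |
| 0.2 | 0/4/6 | 71.4% | 77.9% | 6.5 |
| 0.4 | 0/2/3 | 78.4% | 79.4% | 1.0 |
| 0.4 | 0/4/6 | 75.7% | 79.4% | 3.7 |
| 0.5 | 0/2/3 | 81.7% | 82.4% | 0.7 |
| 0.5 | 0/4/6 | 79.8% | 82.4% | 2.6 |

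**The case against.** The best defence is that the text is open. Section 9.5.1 (Primary Outcome) describes a proposal, lists only the main variables, and looks ahead to an updated final analysis plan. Nothing in it forbids a visit term, so one cannot conclude that the final model lacks it. That stands. But the changes foreseen there are normalizing transforms or non-parametric methods, if the model proves not feasible on blinded data. A model without visit is entirely feasible, so that check would not supply the term.

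The training battery and the baseline at each session are real safeguards. A reader might infer that practice effects pass wholly into the error; they do not, because the session baseline removes part of any shift. How large that part is cannot be read from the protocol, which gives no slope.

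The 6.52 comes from an ANCOVA on the earlier trial. If that model also had no visit term, the SD may already contain visit variation, and planned power would not fall below 80% on this account. The term would then gain precision over the plan.

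A reader might also infer that dropout confounds treatment with visit. The documents do not support this. With 66 subjects, 10% random dropout and shifts of 0/4/6, simulation without the visit term gave a mean estimate of 2.445 against a true 2.45, and a type I error of 3.0%. Chance imbalance in a single trial, or dropout related to treatment, could do harm, but nothing in the protocol points to the latter.

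**Conclusion.** The point holds as one of precision and clarity. The design is balanced over visits, visit is not named in the primary model, and 'time' is undefined. In balanced data the omission neither biases the treatment contrast nor inflates type I error; it makes the test conservative.

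The loss is about 1 to 2 power points for visit shifts of 0/2/3 hits, about 3 to 7 points for 0/4/6, and nil without practice effects. These figures assume two-sided 0.05, 60 subjects, 6.52 as the within-subject SD of one assessment, and a session share of 0.2 to 0.5. The visit shifts and the share are assumptions. Shifts of 0/4/6 are large: the third-visit shift is 6/2.45 = 2.4 times the effect sought. The change is still worth making, because it is nearly free and the trial is planned at only 80% power.

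**What to change.** In section 9.5.1 (Primary Outcome), list the fixed effects as treatment, visit (1, 2, 3), post-consumption assessment time (40 or 120 minutes) and session baseline, with the treatment-by-assessment-time interaction if it is kept. Retain the random subject intercept. State that 'time' means the post-consumption assessment and is separate from visit.

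Apply the same to the secondary models. Where an outcome has one post-consumption measurement, as Doppler flow does at 90 minutes, visit enters and the assessment-time factor falls away.

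The cost is one line of text and 2 degrees of freedom: in the session-mean analysis above, residual degrees of freedom go from 2 × 60 − 3 = 117 to 115. A sequence term is not needed for this purpose. Six sequences would take 5 further degrees of freedom between subjects and, with a random subject intercept, would add little to the within-subject contrast. The change should be fixed before the code is broken.
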